### Sampling

In Phase 2, the sampling will be based on the similar list of flats and households used in Phase 1, i.e. the two PPR flats with the highest and second-highest number of housing units. A total of fourteen flats, seven each for intervention and comparison groups, will then be chosen using a simple random sampling. Cluster randomisation will be performed to reduce the chance of contamination. Each flat is a cluster unit. Since the area of PPR flats in Kuala Lumpur is classified into four zones, residents from two zones will be randomly selected as intervention groups while another two zones as comparison groups. Then, by using the list of households with children aged 3 to 5 years old from the seven targeted flats in the respective zones, household visits will be carried out again to conduct anthropometric measurements on the children to obtain a list of households with undernourished children. After that, the mother-child dyads from the list who meet the inclusion and exclusion criteria will be number coded by the researcher and randomly selected to participate in the present study. The randomization process will be conducted using a computer-generated software (www.randomizer.org) by an independent third party. Participants (n = 82) will be randomized using permuted block randomization into two groups: intervention or comparison group in a 1:1 ratio.

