### Study design

This is a mixed-method study that involves both qualitative and quantitative methods. In phase one of the study, a qualitative research method will be used while in phase two, a two-armed cluster RCT will be conducted. The primary outcome of the RCT study will be weight-for-age z-score (WAZ), while the secondary outcomes will include height-for-age z-score (HAZ), weight-for-height z-score (WHZ), nutrient intake, diet quality, food security status and nutritional knowledge of mothers. The study population includes 3 to 5 years old children with their mothers who live together in the low-cost PPR flats in Kuala Lumpur. Children aged 3 to 5 years old are recruited because when compared to younger children (<2 years old), older children are at higher risk of undernutrition [32].

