#### Phase 2 (quantitative study)

A two-armed, cluster randomised controlled trial will be carried out to determine the effectiveness of a nutrition programme. The selection criteria for respondents in this phase will be almost similar to those in Phase 1, except for one criterion related to children. In Phase 2, only undernourished children (either underweight, stunting, or wasting) aged 3 to 5 years old will be recruited to evaluate the effectiveness of the intervention programme in this particular group. The WHO Child Growth Standards for children under 5 will be used to classify children into underweight (WAZ< -2SD), stunting (HAZ< -2SD) and wasting (WHZ< -2SD) [36]. The exclusion criteria in Phase 2 are similar to the exclusion criteria in Phase 1.

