### Implementation of intervention

For the intervention group, a nutrition programme consisting of an education session with peer-led cooking session and rehabilitation session will be provided. The programme will be known as the Nutrition Education and Rehabilitation Session (NERS). It is planned as a 3-month intervention with a total of 12 sessions, each session lasting for two hours for one day in a week, making up a total of four days in one month. The two-hour session consists of half-an-hour of education lesson followed by one and a half-hour of peer-led cooking session. The rehabilitation session will constitute the remaining days before the next education session. The overall education session will be conducted by the researcher. However, the cooking session will be led by volunteers who are recruited from the PD families in the initial stages of the study. Peer-led cooking session will encourage the involvement and active interaction from the volunteers to assist participating mothers in the food preparation processes for child feeding. The participating mothers will need to bring along their undernourished children during this session and feed their children with the prepared meals when they finish cooking. During the process, volunteered mothers from PD family are encouraged to share their knowledges of preparing food and child feeding to the participating mothers to enhance the PD effect. Five to six mothers will be assigned in a group to prepare meals for five to six children. Each group will be assigned with one volunteer to help them throughout the process. Fresh ingredients will be provided. The meal in each cooking session will be prepared according to the pre-planned NERS menu and will be fed as a snack or additional meal to children. This programme will also include a growth monitoring session whereby the participating mothers weigh their children during each session of NERS before the start of the education session. A weighing scale will be provided by the researcher. Mothers will be trained to weigh their children so that they can monitor their children’s nutritional status.

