#### Primary outcome

Anthropometric measurements of the children will be performed by the researcher. The height of the children will be measured to the nearest 0.1 cm by using a SECA Body Meter 213 (SECA, Germany). Weight will be measured to the nearest 0.1 kg by using a TANITA Digital Weight Scale HD662 (TANITA Corporation, Japan). The collected anthropometric data will be entered and analysed by using the WHO Anthro Survey Analyser [41]. Z-score for weight-for-age (WAZ) will be calculated and underweight (WAZ<-2 SD) children will be identified according to the WHO Child Growth Standards for children under the age of 5 [36].

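### The Sampling section gives two incompatible allocation procedures; on the cluster one, children are screened, judged eligible and selected after their zone's arm is fixed, which leaves a route to selection bias

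*Protocol article*

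**What the plan says.** The Abstract, the Study design section and the Phase 2 section call the trial a two-armed cluster randomised trial. The Sampling section makes each flat a cluster, with seven flats per arm, and says that "residents from two zones will be randomly selected as intervention groups while another two zones as comparison groups".

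The next sentence fixes the order of the field work. It begins "Then, by using the list of households with children aged 3 to 5 years old from the seven targeted flats in the respective zones" and continues that "household visits will be carried out again to conduct anthropometric measurements on the children to obtain a list of households with undernourished children". After that, dyads who meet the criteria "will be number coded by the researcher and randomly selected to participate in the present study".

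The section closes with two further statements. An independent third party runs the randomisation with web-based software. The 82 participants are randomised 1:1 in permuted blocks.

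On eligibility, the Phase 2 section says that "only undernourished children (either underweight, stunting, or wasting) aged 3 to 5 years old will be recruited", defined by WAZ, HAZ or WHZ below -2 SD. WAZ is also the primary outcome (Study design). The Phase 1 exclusions, among them low maternal literacy, are carried over.

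On roles, the Primary outcome section says "Anthropometric measurements of the children will be performed by the researcher", and Implementation of intervention says "The overall education session will be conducted by the researcher". The ethics section has the researcher explain the study to participants.

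**The concern.** Randomising clusters makes the arms comparable only if the people inside the clusters are identified without regard to the arm. Here the zones already have an arm when children are measured against the cut, when exclusions are applied and when dyads are enrolled. Nothing in the article says that the person doing this, or the mothers, are unaware of the arm, or that recruitment closes before the arm is revealed.

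The arms could then differ at entry in severity of undernutrition or in the mothers' motivation and availability. Because the entry cut uses the primary outcome variable, a difference in how borderline children are measured would change baseline WAZ and the amount of regression to the mean at follow-up. An intention-to-treat analysis keeps the groups as enrolled, so it cannot restore comparability lost at enrolment.

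**Working it through.** No stated figure is in dispute. The check sets the statements side by side and then adds a labelled illustration.

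**1. Order of steps (Sampling).** (a) Two zones are drawn for each arm. (b) Household visits follow in the flats of those zones, to measure children and list the undernourished. (c) Eligible dyads are coded by the researcher and selected at random. The sequence is given in the text itself, so allocation comes before screening, eligibility and selection.

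**2. The conflicting sentence.** If 82 individuals are randomised in permuted blocks, allocation comes after step (c). The two accounts cannot be combined: once a dyad lives in an intervention zone, there is nothing left for an individual draw to decide. Three things favour the cluster account. The design is named so throughout. Contamination is the stated reason for randomising clusters. The sample size includes a design effect, which reproduces: 1 + (10 - 1) × 0.03 = 1.27.

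**3. Who does what.**
- Measures the children: the researcher (Primary outcome). The Sampling section does not name who makes the screening visits.
- Codes the eligible dyads: the researcher (Sampling).
- Explains the study: the researcher (ethics section).
- Teaches in the intervention arm: the researcher (Abstract; Implementation of intervention).
- Runs the random draw: an independent third party (Sampling).

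That the researcher knows the arm is an inference from these combined roles, with whole zones already allocated. It is not stated.

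**4. Which steps the safeguards cover.** Random selection acts on the list of eligible dyads, so it prevents hand-picking from that list. It does not govern who is measured below -2 SD, who is excluded on judgement, or who consents once selected. Third-party randomisation protects the draw, not the steps after it.

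**5. Illustration (assumed shifts, no true effect).** Let b be a spurious difference between arms in mean WAZ, in SD units. With 41 per arm in 7 flats, the mean cluster size is 41/7 = 5.86. With the plan's ICC of 0.03, the design effect is D = 1 + 4.86 × 0.03 = 1.146. The standard error is √(2D/n), which is 0.236 for n = 41 and 0.264 for n = 33 (41 less 20%, same D). The two-sided error of an unadjusted test is 1 - Φ(1.96 - b/SE) + Φ(-1.96 - b/SE):

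| b (SD) | n = 41 per arm | n = 33 per arm |
|---|---|---|
| 0.1 | 7.1% | 6.7% |
| 0.2 | 13.5% | 11.8% |
| 0.3 | 24.5% | 20.7% |

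The values of b are not in the document. The table shows sensitivity, not expected bias.

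**The case against.** The best defence is the last sentence of the Sampling section. If individuals really are randomised after selection, allocation follows enrolment and most of this bias falls away. That stands as far as it goes, and it is why the point is conditional. It does not remove the need to act, because the sentence contradicts the zone allocation in the same section.

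Second, there are real safeguards: a household list as the starting point, a WHO z-score cut-off, random selection of dyads and an independent third party. They narrow the problem. Measurement near the cut, exclusion on literacy and consent remain open.

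Third, WAZ is measured at baseline and repeated measures ANOVA is planned, so a baseline shift need not carry in full into the estimated effect. This stands, and the illustrated error rates apply only to an unadjusted comparison. Differences in motivation would not be removed by using baseline WAZ.

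Some stronger readings are tempting but unsupported:
- A reader might infer that the researcher allocates the zones. The Sampling section gives the randomisation to a third party.
- A reader might infer that mothers consent knowing their arm. The ethics section gives no timing relative to allocation and does not say what mothers are told, so this is probable at most.
- A reader might take the comparison arm to be measurement only. Its mothers also receive the education materials and menus (after data collection, per the Abstract), and incentives are given at each follow-up (Comparison group). Attendance at 12 two-hour sessions still asks something different of the intervention mothers, but the contrast should not be overstated.

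**Conclusion.** The point holds in conditional form. The Sampling section contains two allocation procedures that must be reconciled. If allocation is by cluster, which most of the text supports, the order as written has eligibility and selection, and probably consent, settled after the arm is fixed. A researcher who can be inferred to know the arm carries out several of these steps. The stated safeguards reduce this route to selection bias in WAZ without closing it.

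The size of the bias cannot be computed from the document, and the direction is not known either. Any figure, such as a shift of 0.2 SD, is an assumption for illustration. The conclusion rests on the sequence stated in the Sampling section and on two inferences: that the researcher knows the arm, and that the researcher, who is assigned the anthropometry, also makes the screening measurements.

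**What to change.** State one allocation procedure in the Sampling section and remove the other, naming the unit that is drawn (zone, flat or participant).

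If allocation is by cluster, reverse the order of field work: complete screening, consent, random selection of dyads and baseline measurement in all 14 flats. Only then should the independent third party, who is already part of the plan, reveal the allocation of the clusters. This does not in itself require changing the unit of allocation.

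The cost is a re-ordered schedule: the first flats wait until baseline is complete in all flats. If that wait is not workable, a weaker alternative is to have screening and enrolment done by staff who are unaware of the arm, which may need people other than the researcher.

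If allocation is instead by individual, the text should say so and deal with contamination within flats, which is the stated reason for randomising clusters.

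### The Sampling section gives conflicting units of randomisation (flat, zone, participant); the sample size fits only the flat, and zone allocation would leave about 30% power

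*Protocol article*

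**What the plan says.** The Phase 2 section is clear about the design: "A two-armed, cluster randomised controlled trial will be carried out to determine the effectiveness of a nutrition programme". The Abstract and the Study design section also call it a two-armed cluster trial.

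The Sampling section then describes allocation at three levels within one paragraph:

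- **Flat.** "A total of fourteen flats, seven each for intervention and comparison groups, will then be chosen using a simple random sampling", followed by "Each flat is a cluster unit". Clustering is justified there as a way to reduce contamination.
- **Zone.** Kuala Lumpur's PPR flats lie in four zones, and "residents from two zones will be randomly selected as intervention groups while another two zones as comparison groups". Dyads then come from "the seven targeted flats in the respective zones".
- **Participant.** After dyads have been randomly drawn to take part, the paragraph closes: "Participants (n = 82) will be randomized using permuted block randomization into two groups: intervention or comparison group in a 1:1 ratio".

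The frame is also given in two ways. Phase 2 is said to use a list like that of Phase 1, "i.e. the two PPR flats with the highest and second-highest number of housing units", yet fourteen flats are drawn.

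The Sample size estimation section takes about 10 eligible households per flat cluster, an ICC of 0.03 and a design effect of 1.27, and arrives at 41 per group.

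**The concern.** The unit that is randomised determines how many independent units each arm has, which design effect applies and which analysis is valid. Two teams working from this paragraph could run different trials.

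- If zones are allocated, the arm of every flat and family is already settled. Nothing is left to randomise at the lower levels, and the comparison rests on two zones against two.
- If participants are randomised, neighbours in one flat can be in opposite arms and share recipes and advice. That undoes the reason given for clustering and tends to pull the estimated effect toward zero.
- Only if flats are allocated does the design match the planning calculation, which makes no allowance for variation between zones.

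**Working it through.** **Inputs from the protocol.** Two-sided 5% test, 80% power, 28 per group before inflation, m = 10, ICC = 0.03, 20% non-response, 41 per group (Sample size estimation); 14 flats and four zones (Sampling).

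**The plan's own figures.** Design effect = 1 + (m − 1) × ICC = 1 + 9 × 0.03 = 1.27, as stated. The 41 is matched exactly by adding the two inflations: 28 × (1 + 0.27 + 0.20) = 41.16. How the inflations should be combined is a separate matter and is not used here. What matters is that m is the number of eligible households in a flat, so the calculation treats the flat as the cluster.

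**Implied effect.** The mean and SD behind the 28 are not given, so the standardised difference d is back-solved. With the normal formula, d = √[2 × (1.960 + 0.842)² / 28] = 0.749. With the t distribution, d = 0.762. Both are carried forward.

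**Power for k clusters per arm and n analysed per arm.**
- Mean cluster size m = n/k
- DE = 1 + (m − 1) × ICC
- Noncentrality = d / √(2 × DE / n)
- Degrees of freedom = 2k − 2, with power from the noncentral t distribution
- n = 41, or 41 × 0.8 = 32.8 (about 33) after the planned 20% loss

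The zone-level ICC is not given. Using 0.03 for zones is an assumption, so 0.01 to 0.05 is shown.

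*Zone as unit, 2 v 2: 2 df, critical t = 4.30*

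| n per arm | ICC 0.01 | ICC 0.03 | ICC 0.05 |
|---|---|---|---|
| 33 | 36–37% | 30–31% | 26–27% |
| 41 | 41–42% | 33–34% | 28–29% |

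Worked case: n = 32.8, m = 16.4, DE = 1 + 15.4 × 0.03 = 1.462, noncentrality = 0.749 / √(2 × 1.462 / 32.8) = 2.51, power 30%.

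Even with no correlation within zones (ICC 0), power is only 39–40% with 33 per arm and 46–47% with 41. The main loss comes from having 2 degrees of freedom.

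*Flat as unit, 7 v 7: 12 df, critical t = 2.18, ICC 0.03*

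- n = 32.8: m = 4.69, DE = 1.111, power 75–77%
- n = 41: m = 5.86, DE = 1.146, power 83–84%

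**Randomisation test, for reference.** Two of four zones can be chosen in C(4,2) = 6 ways, so the smallest two-sided p-value is 2/6 = 0.33. For seven of fourteen flats there are 3432 ways, and the smallest is 2/3432 = 0.0006.

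**The case against.** **Zone and flat may be nested stages.** Zones are allocated first, then families are taken from flats within them. This is a coherent procedure, so a reader who infers three mutually exclusive designs goes too far. But under this reading the zone is the randomised unit, the flat is mislabelled as the cluster, and the sample size does not describe the trial. The closing sentence on participants still conflicts outright: it assigns people to the two arms and cannot be read as the earlier draw of dyads.

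**A reader might infer that zone allocation makes a 5% test impossible.** The documents do not support that. The floor of 0.33 applies to a randomisation test, which the Statistical analysis section does not propose; it lists t-tests, repeated measures ANOVA and generalised linear models. A zone-level t-test can reach p < 0.05, but with low power. Likewise, with two zones per arm the programme effect can be separated from zone differences, only very imprecisely.

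**A reader might infer that under participant randomisation the design effect of 1.27 loses all basis.** That also goes too far. The programme is delivered to groups of five to six mothers sharing a volunteer (Implementation of intervention), so outcomes may still cluster in that arm. The justification would change rather than disappear.

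**The zone sentence may be deliberate**, as a stronger barrier to contamination. That is a legitimate preference, but the plan must then name the zone as the unit and accept its power.

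**The two-flat frame may be a misplaced clarification**, with the City Hall list from Phase 1 intended. That is probable, but the text does not say so.

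The CONSORT diagram is not shown here. It might indicate the unit, but it could not cure contradictory text.

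**Conclusion.** The concern holds as an internal contradiction that must be settled before Phase 2 allocation. The participant-level sentence is incompatible with the cluster trial described elsewhere in the article. Zone allocation is compatible with calling the flat a sampling stage, but not with a sample size built on the flat as the randomised cluster.

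On the zone reading, power is roughly 30–34% at ICC 0.03, and 26–42% over the range shown, against the planned 80%. These figures rest on an effect back-solved from 28 per group and on a flat ICC borrowed for zones. The conclusion does not depend on that ICC, since power stays below 50% even at zero.

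The flat is the only unit that agrees with the planning calculation. Even so, with 33 analysed per arm it gives 75–77%, slightly short of the target. The discrepancy in the sampling frame is real but subsidiary.

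**What to change.** Before Phase 2 allocation:

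1. Name the flat as the single unit of randomisation and have the independent third party allocate the 14 flats 7:7.
2. Delete the zone allocation and the sentence randomising participants in permuted blocks. Keep the random draw of dyads within flats, described as selection only.
3. Preferably stratify both the sampling and the allocation of flats by zone, so that each zone has flats in both arms. This replaces the simple random sample of flats, which does not guarantee enough flats in every zone.
4. State the power of this design: about 75–77% with 33 analysed per arm, and 83–84% with 41, at ICC 0.03.
5. State the actual sampling frame for the fourteen flats, probably the City Hall list described under Phase 1.

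**Cost.** A protocol amendment and a new allocation list. No extra participants are needed unless the sponsor wants to recover 80% power after the planned 20% loss.

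**Downside.** Flats of both arms may lie in the same zone. If the sponsor keeps zone allocation for that reason, the plan should name the zone as the unit and restate the power accordingly. If allocation has already taken place, the sponsor should report which unit was used, because the analysis and its interpretation follow from it.

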### Development of materials for intervention

All materials will be developed by referring to the published PD guidelines or education modules obtained from previous PD studies. The materials will also refer to official nutrition-related guidelines such as the Malaysian Dietary Guidelines (MDG) for Children and Adolescents [40] and recipes or menus from the Nutrition Society of Malaysia. The findings related to the PD behaviours and foods from the PD family obtained from FGDs in Phase 1 will also be incorporated into the materials. The tools will be designed in a user-friendly form such as leaflets, infographics, and posters so that the messages can be easily delivered to and understood by the target population, i.e. the mothers.

### Implementation of intervention

For the intervention group, a nutrition programme consisting of an education session with peer-led cooking session and rehabilitation session will be provided. The programme will be known as the Nutrition Education and Rehabilitation Session (NERS). It is planned as a 3-month intervention with a total of 12 sessions, each session lasting for two hours for one day in a week, making up a total of four days in one month. The two-hour session consists of half-an-hour of education lesson followed by one and a half-hour of peer-led cooking session. The rehabilitation session will constitute the remaining days before the next education session. The overall education session will be conducted by the researcher. However, the cooking session will be led by volunteers who are recruited from the PD families in the initial stages of the study. Peer-led cooking session will encourage the involvement and active interaction from the volunteers to assist participating mothers in the food preparation processes for child feeding. The participating mothers will need to bring along their undernourished children during this session and feed their children with the prepared meals when they finish cooking. During the process, volunteered mothers from PD family are encouraged to share their knowledges of preparing food and child feeding to the participating mothers to enhance the PD effect. Five to six mothers will be assigned in a group to prepare meals for five to six children. Each group will be assigned with one volunteer to help them throughout the process. Fresh ingredients will be provided. The meal in each cooking session will be prepared according to the pre-planned NERS menu and will be fed as a snack or additional meal to children. This programme will also include a growth monitoring session whereby the participating mothers weigh their children during each session of NERS before the start of the education session. A weighing scale will be provided by the researcher. Mothers will be trained to weigh their children so that they can monitor their children’s nutritional status.

